### Interventions

#### Operative management

The specific procedure for each patient managed operatively will be determined by the operating surgeon. Any adverse intra-operative and post-operative event will be recorded. All surgical procedures will be done by one of the senior orthopaedic registrars, trauma fellows or the orthopaedic consultants.

Operative time, plate size, data on the tourniquet time, radiation time and complications if any, and the number of times the metaphyseal screws have been exchanged will be recorded in both groups.

#### Post-operative protocol

Post operatively all patients will be supported in a back slab for 2 weeks, with instructions to commence early and immediate full passive and active ROM exercises of the shoulder, elbow, and hand as allowed by pain. After 2 weeks, the back slab will be removed and full mobilisation allowed, unless injuries to the distal ulna or DRUJ require longer immobilisation. Documentation of associated injuries to the DRUJ (distal radioulnar joint) and treatment will be made. Within this protocol, all patients will follow a standardised shoulder, elbow, and wrist motion and strengthening program outlined in a patient instruction sheet. (See appendix).

The following general reviews will be undertaken:Clinical review at **2 weeks**, with wound check and X-rayTelephone review at 6 weeks with DASH and PRWE scoresClinical review at **3 months** – EQ5D, DASH and PRWE scoresClinical review and Xray at **12 months**. EQ5D, DASH and PRWE scores. Patients will be given follow up appointments at each visit (Fig. 1).

### Outcome measures

#### Primary outcome

The PRWE(Patient rated wrist evaluation score) score will serve as the primary outcome measure, to be taken at 6 weeks, 3 and 12 months post intervention [29]. The PRWE is a well validated, self-report questionnaire used in studies of wrist function / injuries, which gives information on pain and function of the wrist joint [30, 31]. It consists of a 15-item questionnaire designed to measure a patient’s wrist pain and disability. It has two subscales (pain and function) and has a score range from 0 (no disability) to 100 (severe disability).In order to evaluate effects of treatments, a minimum difference of 11.5 points is required to signify clinically significant difference [28]. The final PRWE score at the end of 1 year will be used to assess any difference between the 2 groups.

#### Secondary outcomes

The DASH score is to be collected as a secondary outcome, in order to assess function of the whole upper limb, at 6 weeks, 3 months and one year [32]. The DASH score has a range from 0 to 100 with higher scores representing greater disability. Subjects rate task difficulty regardless of hand dominance or affected side, thus reflecting their total upper-extremity disability. Both the DASH and PRWE scores have been shown to be ideal and specific as a research tool for the upper limb [30]. The final DASH score at the end of 1 year will be used for definitive comparison between the 2 groups.The EQ5D (EuroQol) score will also be collected as a secondary outcome measure, at 3 months and one year. This score is a validated measure of health related quality of life, consisting of a 5 health domains as well as a separate VAS (Visual analogue) score. The five domains included in the EQ-5D are: mobility; self-care; usual activities; pain/discomfort and anxiety/depression. The EQ5D is the measure that tends to be most utilised in cost utility analysis [33] . The final EQ5D at the end of 1 year will be used for definitive analysis.Complications (including surgical site infection, unplanned surgery, implant failure, loss of reduction/screw breakout or implant fracture and post-operative nerve palsy up to one year) in both groups will also be documented and compared.Surgical data including operation time and screw numbersRadiographic indices including radial height, tilt and inclination and rates of non-union / delayed union and the Soong score will be analysed and compared in both groups.Soong score will be used to assess prominence and profile of the plate [17].The active range of motion (ROM)at the wrist and grip strength at 3 months and one year will be measured.Time to resumption of work and patient perceived percentage return of global function at 6 weeks, 3 months and 1 year.

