**Methods and Design:**

Patients between the ages of 18 and 80 presenting to the Royal Adelaide Hospital with isolated closed distal radial fractures will be invited to participate in this study. A total of 200 patients are required to provide 90% statistical power at a 5% alpha level to detect a difference of 11.5 points on the PRWE (Patient rated Wrist evaluation) score. The primary outcome measure will be the PRWE score while the secondary outcome measures will include the DASH score, EQ5D score, clinical range of movements, grip strength as well as patient perceived return of function at the wrist and time to resumption to work. These will be measured at 6 weeks, 3 months and 12 months. Radiographic indices including the radial tilt, length, volar inclination and plate prominence will also be measured. Complications will be recorded up to 12 months. Post hoc comparisons will be done using paired t tests. An intention to treat and a per protocol analysis will be done to compare the 2 groups.

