### Sample size

Sample size calculations were based on the requirement that effects be assessed at the 5% alpha level with 90% statistical power. It has been shown that the minimum clinically important difference on the PRWE is 11.5 points [28]. Assuming a standard deviation of 20 points, a sample of 65 patients per group would be required; following the application of a variance inflation factor of 1.5 to account for repeated measurements over time and patient attrition, a sample of 98 patients per group would be required.

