### Statistical analysis plan

Continuous measures will be summarised as means with standard deviations and medians with inter-quartile range. Categorical measures will be summarised as percentages. Treatment effects will be assessed over time using linear mixed effects models with patient treated as a random factor. A normal distribution with an identity link function will be assumed for continuous measures, while a multinomial distribution and cumulative logit function will be applied to ordinal outcomes. An intention-to treat and a per-protocol analysis will be considered. All tests will be two-tailed and assessed at the 5% alpha level.

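### Delayed union is to be compared between plates, but the review schedule as shown has films only at 2 weeks and 12 months, which cannot separate late from timely union

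*Protocol article*

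**What the plan says.** Under Secondary outcomes, the protocol article groups union with the radiographic indices and commits to a between-arm comparison: "rates of non-union / delayed union and the Soong score will be analysed and compared in both groups". It gives no time after which union counts as delayed.

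Under Post-operative protocol, the reviews are listed one by one. An X-ray is named at the 2-week clinical review and at the 12-month clinical review. The 6-week contact is a telephone call for DASH and PRWE. The 3-month clinical review carries "EQ5D, DASH and PRWE scores" and no imaging.

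Two other places bear on the schedule, and neither adds a film. Secondary outcomes adds physical measures at 3 months: "The active range of motion (ROM)at the wrist and grip strength at 3 months and one year will be measured". The abstract says "Radiographic indices including the radial tilt, length, volar inclination and plate prominence will also be measured", without times and without mention of union.

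**The concern.** Delayed union is defined by when a fracture unites, so observing it needs information on union status at or near some intermediate time. The schedule as shown provides none. If it is followed, the only delayed unions on record among fractures healed by 12 months will be those in patients who happened to have an extra film.

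The comparison would then rest partly on who was imaged. Under Randomisation, the surgical team is told which plate to use. The Blinding section covers patients, the researchers collecting the primary outcome and the statistician; it does not mention treating surgeons or those who read the films. Decisions to request extra films could therefore be made with knowledge of the plate. What is at stake is how a stated secondary comparison of a new plate with the standard one can be interpreted.

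**Working it through.** The article states no figure for delayed union, so the check sets the outcome against the film times.

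**Inputs** (Post-operative protocol)
- Scheduled films: week 2 and week 52 (12 months).
- Week 6: telephone, so no film is possible.
- 3 months: in-person review, no film named.
- Threshold for delayed union: not given. Assumed here to lie anywhere from 12 to 26 weeks.

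**Step 1: the gap.** 52 − 2 = 50 weeks without a planned image; 50/52 = 96% of follow-up.

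**Step 2: films near the threshold.** A film within 4 weeks of the threshold T would have to fall in [T − 4, T + 4].
- T = 12: weeks 8 to 16, no scheduled film.
- T = 16: weeks 12 to 20, none.
- T = 24: weeks 20 to 28, none.
- T = 26: weeks 22 to 30, none.

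**Step 3: what the two films can classify.** Let U be the week of union, and take a fracture not yet united at week 2.
- Not united at week 52: U > 52. Non-union at 12 months is observed.
- United at week 52: 2 < U ≤ 52. Every T from 12 to 26 lies inside this interval, so U ≤ T (timely) and T < U ≤ 52 (late) give the same pair of films.

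The result of step 3 does not depend on which T in the range is chosen. It does assume that union is not already established at week 2; the article does not say so, but it has the back slab on until then.

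**Step 4: effect on the primary analysis.** The sample size uses PRWE alone: "the minimum clinically important difference on the PRWE is 11.5 points" and "Assuming a standard deviation of 20 points, a sample of 65 patients per group would be required", with "effects be assessed at the 5% alpha level with 90% statistical power" and two-sided testing ("All tests will be two-tailed and assessed at the 5% alpha level").
- Normal approximation: n = 2 × (1.960 + 1.282)² × 20² / 11.5² = 63.6, so 64 per group.
- Noncentral t: power is 89.8% at 64 and 90.2% at 65, which reproduces the stated 65.
- Inflation: 65 × 1.5 = 97.5, so 98 per group; 2 × 98 = 196, or about 200.

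Nothing here involves union, so the primary calculation and analysis are untouched.

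**The case against.** The strongest reply is that the visit list is not exhaustive. Its 3-month and 12-month lines omit range of motion and grip strength, and its 6-week line omits the patient's own rating of recovered function, yet Secondary outcomes requires all of these at those times. A missing X-ray at 3 months is therefore weaker evidence than it looks. Fig. 1, cited with the schedule, is not shown, and neither is the full protocol (V 1.2) that the article condenses. This stands as a limit on certainty. It does not remove the point: the omitted clinical measures are supplied elsewhere in the article, whereas no other part of the text supplies a film. The list also assigns X-rays to particular visits, so this is more than silence about imaging.

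A second reply is that non-union and delayed union, joined by a slash, may be meant as one category of failure to unite normally. Part of that category, non-union at 12 months, is indeed observable. The other part, fractures that united late, is not, so a combined rate would still be incomplete.

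Third, a reader might infer that the comparison will be biased by arm, or that the recorded delayed-union rate will be almost nil. The article supports neither. It does not say who requests follow-up films or that such requests depend on the plate; patients are blinded, and complications are managed under in-house protocols for all participants. It gives no union times or base rate from which to predict a recorded rate. Differential imaging is possible, not shown.

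**Conclusion.** The point holds for delayed union only, and for the schedule as the text gives it. The article commits to comparing a rate that its two planned films cannot determine in any fracture united by 12 months, because those films leave 50 of 52 weeks unobserved. It would be too strong to say that union outcomes in general cannot be assessed, since the 12-month film can show non-union.

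The conclusion rests on three assumptions: that no further film for all patients appears in Fig. 1 or the full protocol; that union is not established by week 2; and that the delayed-union threshold falls between the two films (12 to 26 weeks was examined). This is a minor issue in a secondary outcome, but it is a mismatch between two stated commitments and not merely missing detail.

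**What to change.** Reconcile Secondary outcomes with Post-operative protocol, after checking Fig. 1 and the full protocol.

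- If a film between 2 weeks and 12 months is already scheduled for all patients, correct the visit list to show it and state how delayed union is defined.
- Otherwise, limit the compared outcome to radiographic union or non-union at 12 months. Report any delayed union found on unscheduled films descriptively, together with the number of unscheduled films in each arm, so that readers can judge how evenly the arms were imaged.

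In either case the change is to wording. No film is added, and care and the primary analysis stay as they are. The cost of the second route is that one secondary rate is no longer formally compared, plus a count of unscheduled films per arm.

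### Time to resumption of work is a censored duration recorded once per patient, but the only stated rule that can cover it is the normal linear mixed model for continuous measures

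*Protocol article*

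**What the plan says.** The Secondary outcomes section of the protocol article lists "Time to resumption of work and patient perceived percentage return of global function at 6 weeks, 3 months and 1 year". The abstract also names "patient perceived return of function at the wrist and time to resumption to work" among the secondary outcomes and adds "These will be measured at 6 weeks, 3 months and 12 months".

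The Statistical analysis plan section gives one approach to treatment effects: "Treatment effects will be assessed over time using linear mixed effects models with patient treated as a random factor". It then sets the distribution by type of outcome. For one type, "A normal distribution with an identity link function will be assumed for continuous measures"; for the other, "a multinomial distribution and cumulative logit function will be applied to ordinal outcomes". On testing it says "All tests will be two-tailed and assessed at the 5% alpha level".

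The section does not mention time to resumption of work, a time-to-event method, or a censoring rule. Eligibility (Table 1) runs from age 18 to 80 with no employment criterion, and the last review is at 12 months.

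**The concern.** A return-to-work time is a duration. It is not ordinal, so of the two distributional rules only the normal one can apply. Two features make that rule unsuitable.

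- **One value per patient.** The visits at 6 weeks, 3 months and 1 year are occasions for finding out whether the patient has returned. The return time itself is a single number, so a model over time with a patient random effect has no repeated measure to use.
- **Right-censoring.** For a patient not back by 12 months, or lost earlier, all that is known is that the time exceeds the last contact. A normal model for observed values has no place for that information. The Sample size section itself allows for attrition.

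The outcome is also undefined for people not working before injury, so the analysis population needs stating.

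At stake is the plate comparison on this one secondary outcome. If only observed times enter, the analysis conditions on having returned, which is itself affected by the speed of recovery.

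**Working it through.** **The plan's own figures.** The article states no rate, effect size or sample size for this outcome. The power statement ("effects be assessed at the 5% alpha level with 90% statistical power") leads to a calculation for the PRWE only: a difference of 11.5 points with SD 20 needs 64 to 65 per group, and 65 × 1.5 = 97.5, or 98. That reproduces and does not bear on this point.

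**Assumptions.** Return times are exponential with mean m months, there is no loss before 12 months, and all patients counted were working before injury. None of the means comes from the documents.

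**Formulas**, with q = exp(−12/m), the share not back at 12 months:

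- mean among returners only: m − 12q/(1 − q)
- restricted mean to 12 months, all patients: m(1 − q)

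The restricted mean is the benchmark because 12 months of follow-up can estimate it. The unrestricted mean would need extrapolation.

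| Mean m (months) | q | Returners-only mean | Restricted mean |
|---|---|---|---|
| 2 | 0.002 | 1.97 | 2.00 |
| 3 | 0.018 | 2.78 | 2.95 |
| 4 | 0.050 | 3.37 | 3.80 |
| 6 | 0.135 | 4.12 | 5.19 |
| 5 | 0.091 | 3.80 | 4.55 |
| 7 | 0.180 | 4.36 | 5.74 |

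Differences, taken before rounding:

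| Arms | Not back at 12 months | Returners only | Restricted mean | Ratio |
|---|---|---|---|---|
| 2 vs 3 | 0.2% vs 1.8% | 0.81 | 0.95 | 0.85 |
| 4 vs 6 | 5% vs 14% | 0.75 | 1.39 | 0.54 |
| 5 vs 7 | 9% vs 18% | 0.56 | 1.19 | 0.47 |

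**Direction.** Shrinkage is not guaranteed. Count a non-returner as 52 weeks.

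- Returners average 10 vs 8 weeks, and 5% vs 15% never return. Returners only: 10 − 8 = 2.0 weeks in favour of the second arm. All patients: 0.95 × 10 + 0.05 × 52 = 12.1 against 0.85 × 8 + 0.15 × 52 = 14.6, so 2.5 weeks against it. The sign reverses.
- The same returner means, with 5% not returning in each arm. Returners only: 2.0 weeks. All patients: 12.1 − (0.95 × 8 + 0.05 × 52) = 12.1 − 10.2 = 1.9 weeks. Leaving non-returners out slightly enlarges the difference.

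**Power.** Simulation used 2,000 trials per setting, exponential times, a hazard ratio for return of 1.5 and a cut-off at 52 weeks. The 60 workers per arm is an assumption.

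| Slower arm not back | t test, returners only | Log-rank | t test, non-returners set to 52 weeks |
|---|---|---|---|
| 2% | 0.52 | 0.60 | 0.59 |
| 10% | 0.29 | 0.56 | 0.54 |
| 20% | 0.18 | 0.54 | 0.50 |

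With 98 per arm and 10% not back, the three powers are 0.46, 0.77 and 0.75. Under no plate effect, all three tests rejected in about 5% of trials.

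**The case against.** The strongest reply is that this rests on silence. Only the article is at hand, and a survival method and censoring rule for one of many secondary outcomes are ordinary content of a separate analysis plan. The section also gives no model for binary outcomes, although complications are to be compared. It may therefore have been written for the repeated scores and never meant for this outcome. That limits the point: the absence of a survival method is not itself the finding. What remains is that the article fixes a distribution by type of outcome, and the only type that admits a duration carries an unsuitable model.

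A reader might infer that the plan drops patients not back at work. The documents do not say so, and a linear model does not force it. Such patients could be set to 12 months, which keeps most of the log-rank power in the simulation, and the section mentions an intention-to-treat analysis. However, no such rule is stated, and it would not deal with patients lost earlier.

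A reader might also infer that any plate difference is shrunk. That is false in general, as the reversal and the slight enlargement above show.

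Two further objections stand. When few patients are still off work at 12 months, the loss is modest. And leaving out people not working before injury adds no bias, because work status is a baseline trait; it only needs defining.

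**Conclusion.** The point holds in a limited form. The only stated rule that can cover time to resumption of work does not suit a once-per-patient, right-censored duration. The consequence is conditional: it arises if only observed times are analysed. The returners-only difference is then 85% of the restricted-mean difference when under 2% are not back, and about half (54% and 47%) in the two settings with 5% to 18% not back. With non-return that differs between plates, it can point the wrong way.

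These sizes rest on assumed exponential times and assumed rates; the article supplies neither. The primary PRWE analysis and the sample size are unaffected, and the simulations show no inflation of type I error. This is a minor improvement to a secondary outcome.

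**What to change.** In the Statistical analysis plan section, exempt time to resumption of work from the normal-model rule and state:

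- **Population:** patients working before injury.
- **Censoring:** at last contact or 12 months, whichever is earlier.
- **Analysis:** Kaplan-Meier curves by plate, with a log-rank test or Cox model stratified by the age and sex randomisation strata. Restricted mean time to 12 months is an alternative.

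If a separate analysis plan already says this, a cross-reference is enough.

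The cost is a sentence or two of analysis wording and recording of pre-injury work status on the case report form. No extra visits or patients are needed.

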### Data management

The case report forms will be designed by the trial coordinator in conjunction with the trial management team. All patient identifiable information will be held in accordance with the GCP (Good clinical practice) guidelines. Participants will be identified by a trial number and a hospital ID number. The deidentified data will be entered in an electronic format by the research assistant in an EXCEL format, who will also coordinate the follow up visits and collection of the patient filled data forms. The data will be kept in a secure electronic form on a password protected hospital computer, and will be destroyed 15 years after the completion of the study.

### Statistical analysis plan

Continuous measures will be summarised as means with standard deviations and medians with inter-quartile range. Categorical measures will be summarised as percentages. Treatment effects will be assessed over time using linear mixed effects models with patient treated as a random factor. A normal distribution with an identity link function will be assumed for continuous measures, while a multinomial distribution and cumulative logit function will be applied to ordinal outcomes. An intention-to treat and a per-protocol analysis will be considered. All tests will be two-tailed and assessed at the 5% alpha level.

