### Consent procedures

Recruitment and consenting will be done by a trained research associate who will present the trial and interventions in a consistent and unbiased manner. Eligible patients will be provided with an information sheet and will have time to discuss their concerns prior to enrolment. (Patient Booklet and participation form-Additional file 1).

Inclusion Criterion and exclusion criterion are as shown in Table 1. Patients with isolated injuries in the upper limb were chosen so as to avoid the effect other injuries in the same limb could have and therefore bias the outcome. As most of the questionnaires are self-explanatory and to be filled in by patients themselves, reasonable proficiency in English is a pre-requisite.

**Table 1 Tab1:** POWIFF trial - Inclusion and exclusion criterion

Inclusion Criterion	Exclusion criterion
1. Age-18-80	1. Patients with concomitant injuries affecting treatment and rehabilitation of the affected arm
2. Pre-operative DASH score of 30 or less	2. Patients with associated neurovascular injuries requiring immediate surgery
3. Isolated closed distal radius fracture with shortening of radius of more than 3 mm, dorsal radial tilt of more than 10 degrees and an intra articular step of more than 2 mm.	3. Patients with associated significant carpal injuries, including scaphoid fractures
	4. Patient unlikely or unhappy to attend for follow up
	5. Patient with limited English proficiency
	6. Patient without cognitive capacity to consent and participate
	7. Patients with impaired upper limb function prior to injury enough to have a DASH score of more than 30 points

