### Randomisation

Allocation of trial treatments will be provided through the local statistics department by a statistician who is not the trial statistician. Randomisation will be a 1:1 allocation using a computer generated randomisation schedule (using Stata Statistical Software: Release 14. College Station, TX: StataCorp LP) stratified by age and sex (four strata) using permuted blocks of size four. A seed was used as the random number generator to specify unique subject identifiers. The patient after being considered eligible for the study and consented by the orthopaedic trainee is stratified according to age and sex. The trainee then informs one of the coinvestigators who obtains the randomisation number from the previously generated schedule. The surgical team will be informed of the plate to be used, once randomised.

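### Randomisation is stratified by age and sex, but the stated mixed model names no stratum terms, so its standard error is somewhat too large and its test mildly conservative

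*Protocol article*

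**What the plan says.** All places are in the protocol article.

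- **Randomisation:** allocation is 1:1, "stratified by age and sex (four strata) using permuted blocks of size four".
- **Statistical analysis plan:** "Treatment effects will be assessed over time using linear mixed effects models with patient treated as a random factor". The section goes on to fix the distribution and link, mentions intention-to-treat and per-protocol analyses, and adds: "All tests will be two-tailed and assessed at the 5% alpha level". It gives no list of fixed effects. Age, sex, stratum and baseline scores are neither included nor excluded.
- **Sample size:** the target is that "effects be assessed at the 5% alpha level with 90% statistical power". No allowance is made for covariate adjustment.
- **Consent procedures, Table 1:** one inclusion criterion is "Pre-operative DASH score of 30 or less". The matching exclusion criterion describes arm function before the injury.
- **Post-operative protocol and Outcome measures:** PRWE and DASH are scheduled at 6 weeks, 3 months and 12 months. No baseline PRWE is scheduled, and a baseline DASH is not listed as a data item.

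**The concern.** Stratified blocking makes the arms nearly equal in age group and sex. If those factors predict the PRWE, this balance lowers the true sampling variance of the difference between arms. A model without the factors cannot recognise that. It leaves the stratum variance in the patient and residual terms and reports a standard error for a trial with no such balance. The patient random effect does not help: treatment is compared between patients, and that effect simply absorbs the stratum differences.

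The consequences are a confidence interval wider than the design warrants and a test that rejects less often than its nominal 5%. The direction is conservative.

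The eligibility DASH raises a different and weaker matter. It is not a randomisation factor, so leaving it out does not make the standard error wrong. Including it could only make the estimate more precise.

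**Working it through.** **Inputs from the article.** Two-sided alpha 5%, power 90%, difference 11.5 points ("the minimum clinically important difference on the PRWE is 11.5 points"), SD 20, inflation factor 1.5 ("a variance inflation factor of 1.5 to account for repeated measurements over time and patient attrition"), four strata, blocks of four.

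**Assumed input.** R², the share of 12-month PRWE variance explained by the strata. The documents do not give it, so 0, 5% and 10% are shown.

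**1. The plan's own figure.** The article says: "Assuming a standard deviation of 20 points, a sample of 65 patients per group would be required".
- Normal approximation: n = 2(1.960 + 1.282)² × 20² / 11.5² = 63.6, so 64 per group. The t-test version gives 64.5, so 65.
- 65 × 1.5 = 97.5, so 98 per group.

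Both stated figures reproduce.

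**2. Reported and true standard error at 98 per group.** Without stratum terms, the reported SE is 20 × √(2/98) = 2.86. With the strata fully balanced, the true SE is 2.86 × √(1 − R²).

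**3. True type I error without stratum terms.** 2 × [1 − Φ(1.96 / √(1 − R²))].

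| Strata R² | Reported SE | True SE | 1.96/√(1 − R²) | Type I error |
|---|---|---|---|---|
| 0 | 2.86 | 2.86 | 1.960 | 5.0% |
| 5% | 2.86 | 2.79 | 2.011 | 4.4% |
| 10% | 2.86 | 2.71 | 2.066 | 3.9% |

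**4. Is the stated power at risk?** Take 65 per group, the number before inflation. The reported SE is s = 20 × √(2/65) = 3.508, and the true SE is t = s√(1 − R²).
- Power without stratum terms: Φ((11.5 − 1.96s)/t).
- Power with stratum terms: Φ((11.5 − 1.96t)/t).

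| Strata R² | t | Power without strata | Power with strata |
|---|---|---|---|
| 0 | 3.508 | 90.6% | 90.6% |
| 5% | 3.419 | 91.2% | 92.0% |
| 10% | 3.328 | 91.8% | 93.3% |

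Power stays above 90% either way. Leaving out the strata forgoes a point or so.

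**5. Simulation check.** 10,000 null trials per scenario, 196 patients, blocks of four within four strata (assumed to hold 20%, 15%, 15% and 50% of patients), 12-month comparison only. The adjusted model contains the strata and DASH. Monte Carlo error of a 5% rate: √(0.05 × 0.95/10,000) = 0.2 percentage points.

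| Scenario | Model | Mean reported SE | Actual SD of estimate | Type I error |
|---|---|---|---|---|
| Strata R² 10%, DASH 0 | unadjusted | 2.85 | 2.71 | 3.9% |
| | adjusted | 2.72 | 2.71 | 4.9% |
| Strata 0, DASH R² 10% | unadjusted | 2.86 | 2.88 | 5.3% |
| | adjusted | 2.72 | 2.73 | 5.0% |

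Ignoring the strata gives a reported SE that exceeds the true one. Ignoring DASH gives an SE that agrees with the true one within simulation error, only larger than it need be.

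**The case against.** The strongest reply is that the analysis section is silent on fixed effects and does not rule out adjustment. The article condenses a full protocol (version 1.2), and a covariate list is the kind of detail often left to a fuller document. This stands in part. A reader might infer that the trial has decided against adjustment, and the text does not support that. But the section does more than defer: it fixes the model class, random factor, distribution, link, sidedness and alpha level. Set beside the stated randomisation, that model lacks the terms the design calls for. If a fuller plan already has them, confirming it costs nothing.

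Three stronger readings are tempting and are not supported.

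- **That omitting DASH also invalidates the standard errors.** It does not, because DASH was not used in the randomisation.
- **That a usable baseline DASH is already in the trial data for everyone.** The eligibility cut-off implies that a value is obtained, but no section schedules it as a data item. Table 1 also places it before surgery in one criterion and before injury in another.
- **That adjustment would bring a large, known gain.** Any gain depends on an R² the documents do not give. At R² = 0 nothing is lost by omission.

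It is also fair to say that the calculations treat one 12-month comparison, not the full repeated-measures model. The mechanism is the same there, because treatment remains a between-patient contrast.

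**Conclusion.** The point holds for the stratification factors. Fitted as written, the model overstates the standard error of the treatment contrast: at 98 per group it reports 2.86 where the true value is 2.79 or 2.71, for an assumed strata R² of 5% or 10%. The test then runs at about 4.4% or 3.9% instead of 5%. If the strata explain nothing, there is no effect.

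These figures rest on the assumed R², the article's SD of 20, near-complete balance within strata, and no stratum terms being added elsewhere. There is no bias and no excess of false positives, and the stated 90% power is reached without adjustment. This is a modest mismatch between design and analysis that is free to repair, and it does not threaten validity.

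For DASH there is an optional efficiency gain only. It may be small, because eligibility confines the score to 0–30.

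**What to change.** **Stratification factors.** Add to the Statistical analysis plan section: the mixed models for 12-month PRWE and for the continuous secondary outcomes include the age group and sex used in the stratified randomisation as fixed effects, and the estimate without them is reported as a sensitivity analysis. This costs one sentence. The strata are known for every randomised patient, so no new data are needed. The terms should be fixed before outcome data are seen, so that adjustment cannot be chosen by its result.

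**DASH, separately and as an efficiency gain.** List the DASH value used for eligibility as a recorded data item, state whether it refers to function before the injury (reconciling the two entries in Table 1), and enter it as a continuous covariate. This costs one field on the case report form and one further clause in the model statement.
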